#### Procedure for unblinding if needed {17b}

In this open-label trial, no unblinding needs to be performed.

### Data collection and management

#### Plans for assessment and collection of outcomes {18a}

The primary and secondary endpoints of our trial are mainly based on the scales of the SAQ. These include evaluation of QoL, physical limitation, angina stability, angina frequency, treatment satisfaction, and disease perception. The SAQ is the most widely used and extensively validated patient-reported measure of outcome for AP. Originally derived from a mostly male cohort [18], it has since also been validated for women [20–23]. The SAQ scores were shown to correlate with physiological metrics of coronary dysfunction and to be of prognostic value in patients with obstructive CAD [4, 21, 22].

Dyspnea is not part of the definition of angina pectoris; however, a substantial part of patients with CAD present with dyspnea as the dominant symptom together with atypical chest pain [24]. We additionally investigate changes of the NYHA classification at the time of both follow-ups. This classification has been widely used to assess dyspnea especially in the setting of heart disease and is part of the evaluation recommended in the current guidelines [2].

Data collection also includes clinical baseline parameters such as age, sex, complaints, severity of CAD, left ventricular ejection fraction, heart frequency, blood pressure, and medication.

#### Plans to promote participant retention and complete follow-up {18b}

The participants will be contacted via telephone for the 1- and 6-month follow-up. The participants will not receive monetary compensation.

#### Data management {19}

Data entry is performed both on the case report form and an electronic database. To ensure optimal quality control regarding GCP-compliant data management, monitoring, and biometry, the Centre for Clinical Studies at the University Hospital Regensburg is part of the trial.

#### Confidentiality {27}

All study-related information will be stored securely at the study site. All participant information will be stored in locked file cabinets in areas with limited access. All reports, data collection, process, and administrative forms will be identified by a coded ID (identification) number only to maintain participant confidentiality. All records that contain names or other personal identifiers, such as locator forms and informed consent forms, will be stored separately from study records identified by code number. All local databases will be secured with password-protected access systems. Forms, lists, logbooks, appointment books, and any other listings that link participant ID numbers to other identifying information will be stored in a separate, locked file in an area with limited access.

#### Plans for collection, laboratory evaluation, and storage of biological specimens for genetic or molecular analysis in this trial/future use {33}

No biological specimens are collected for this study.

### Statistical methods

#### Statistical methods for primary and secondary outcomes {20a}

The primary and all secondary endpoints will be analyzed by using an analysis of covariance (ANCOVA) with treatment group and sex as fixed factors and baseline measurement of the dependent variable, number of implanted stents, and baseline of Canadian Cardiovascular Society score as covariates. All analyses will be performed by using the intention-to-treat population. Patients with missing data in one of the endpoints will be excluded from the respective analysis.

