**Design and methods:**

The PLA-pCi-EBO-pilot-trial is a prospective, multi-center, randomized, controlled investigator-initiated pilot trial to study the effect of visual demonstration of successful PCI on quality of life (QoL) and angina pectoris (AP) in patients with symptomatic stable CAD/CCS. All patients with stable CAD/CCS and successful PCI will be screened. One hundred forty four patients with a frequency of AP ≥ 2/week will be randomized 1:1 stratified for AP frequency > 1/day. The control group will receive the common written procedural report on the procedure. Patients in the intervention group will additionally be given a printout picture of their coronary angiogram both before and after PCI. Primary endpoints are change in the Seattle Angina Questionnaire (SAQ)-derived QoL score 1 and 6 months after PCI. Secondary endpoints are changes in other SAQ-derived scores and dyspnea (NYHA score) 1 and 6 months after PCI.

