## Methods: participants, interventions, and outcomes

### Study setting {9}

Patients will be recruited in Germany from different clinical settings including a university hospital, a community hospital, and a cardiological clinic.

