#### Sample size {14}

The study is designed and powered as a pilot trial to allow for precise parameter estimation for a subsequent confirmatory study. There is sparse comparable data to calculate effect size estimations for the kind of intervention employed in our study. However, clinical observation suggests that our pragmatic approach of influencing AP frequency by the simple means of visual demonstration of the angiographic result of PCI has a strong effect on the patients. The ISCHEMIA trial revealed relevant symptomatic improvement in patients with more severe AP [19]. Placebo- and sham-controlled trials have shown that large parts of the treatment effect of conservative and interventional therapeutic strategies for AP can be ascribed to context factors such as the one employed in this pilot study. Thus, we think it is reasonable and realistic to expect a difference of 10 points with a standard deviation of 20 between the control and interventional groups regarding the quality of life scale of the SAQ (effect size of *d* = 0.5 (medium effect)). This difference would also be highly clinically relevant. To show an effect size of *d* = 0.5 with a power of 80% (*β* = 0.2) at a two-tailed significance level of *α* = 0.05, *n* = 64 patients need to be included in each group. With an estimated drop-out rate of 10%, a total of *n*_total_ = 144 patients need to be recruited.

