### Assignment of interventions: allocation

#### Sequence generation {16a}

Patients who fulfill the inclusion and exclusion criteria will be randomized in a 1:1 ratio stratified for daily or not daily AP episodes by a computer-generated random number list.

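### The ANCOVA leaves out the angina-frequency factor used to stratify randomisation, and the article defines that factor in two ways

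*Protocol article*

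**What the plan says.** Statistical methods {20a} gives one model for the primary endpoint and all the secondary ones: an "analysis of covariance (ANCOVA) with treatment group and sex as fixed factors and baseline measurement of the dependent variable", with the number of stents and the baseline Canadian Cardiovascular Society score as further covariates. The list reads as complete, and angina frequency as used for stratification is not on it.

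Three places describe the stratification:
- Abstract, Design and methods: patients "will be randomized 1:1 stratified for AP frequency > 1/day".
- Participant timeline {13}: strata are daily against not daily angina.
- Sequence generation {16a}: patients are "randomized in a 1:1 ratio stratified for daily or not daily AP episodes".

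No other stratification factor is named, and no block size is given.

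Sample size {14} assumes "a difference of 10 points with a standard deviation of 20 between the control and interventional groups" on the SAQ quality-of-life scale, 80% power and a "two-tailed significance level of *α* = 0.05". It arrives at 64 evaluable patients per arm, or 144 recruited with 10% drop-out. The same section and the Discussion say that the pilot is meant to supply parameter estimates for a later confirmatory trial.

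**The concern.** A factor judged important enough to stratify on would normally be in the analysis model. Here the model adjusts for sex, stents and Canadian Cardiovascular Society score, none of which was stratified on, and omits the one factor that was. For the primary endpoint the baseline covariate is the quality-of-life score, not angina frequency, so the stratum does not enter by that route either.

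Two things could follow if the stratum carries information about outcome beyond the listed covariates:
- Its share of the variance stays in the residual. The treatment estimate is less precise than it could be, and the residual SD handed to the confirmatory trial is too large.
- If the allocation list also forces balance within strata, the treatment estimate varies less than the model's standard error implies. Intervals are then somewhat wide and the test somewhat conservative.

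Separately, the two definitions are incompatible at one point. A patient with exactly one episode a day is in the lower stratum under the Abstract's cut-off and in the daily stratum under the Methods wording. The stratum cannot be put into a model until it is clear which definition drew the envelopes.

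**Working it through.** **Inputs from the article (Sample size {14}).** Difference 10, SD 20, two-sided α 0.05, power 80%, 64 per arm, drop-out 10%.

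**Assumptions, not in the article.** R² is the share of the variance left after the listed covariates that the stratum explains. It is varied from 0 to 0.20. The SD of 20 is taken as the SD after the listed covariates but before the stratum. The simulation also assumes that 40% of patients have daily angina.

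**Step 1: reproduce the stated sample size.** The normal approximation gives 2 × (1.960 + 0.842)² × (20/10)² = 62.8, so 63 per arm. The exact t test needs 64 per arm (power 80.1%). Then 64/0.9 = 71.1, so 72 per arm and 144 in total. The stated figure reproduces and does not depend on the stratum.

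**Step 2: balance within strata (for example, blocking).** The model that omits the stratum reports SE = 20 × √(2/64) = 3.536. The true SE is 3.536 × √(1 − R²). Hence:
- Ratio of reported to true SE = 1/√(1 − R²)
- Actual type I error = 2 × [1 − Φ(1.96/√(1 − R²))]
- Power, stratum omitted = Φ[(10 − 1.96 × 3.536) / (3.536 × √(1 − R²))]
- Power, stratum included = Φ[10 / (3.536 × √(1 − R²)) − 1.96]

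| Assumed R² | SE too wide by | Type I error | Power omitted | Power included | Points forgone |
|---|---|---|---|---|---|
| 0 | 0% | 5.0% | 80.7% | 80.7% | 0 |
| 0.02 | 1.0% | 4.8% | 81.0% | 81.5% | 0.5 |
| 0.05 | 2.6% | 4.4% | 81.4% | 82.7% | 1.3 |
| 0.10 | 5.4% | 3.9% | 82.0% | 84.6% | 2.6 |
| 0.20 | 11.8% | 2.8% | 83.4% | 88.5% | 5.1 |

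**Step 3: no blocking within strata.** Chance imbalance between arms then adds to the variance of the estimate, and the omitted model's SE of 3.536 is correct. Type I error stays at 5%. Power is 80.7% without the stratum against 81.5%, 82.7% and 84.6% with it at R² of 0.02, 0.05 and 0.10. That is 0.8, 2.0 and 3.9 points forgone, ignoring the small cost of estimating one more term. These losses cannot be combined with the type I figures of step 2, because the two rest on opposite assumptions about balance.

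**Step 4: simulation check.** N = 128, with 8,000 replicates under the null and 4,000 under the alternative. At R² = 0.10:
- Blocks of 4 within strata, stratum omitted: mean model SE 3.53, empirical SD 3.34, type I error 0.037. With the stratum included: 3.35, 3.34 and 0.049.
- Unblocked within strata, stratum omitted: mean model SE 3.54, empirical SD 3.52, type I error 0.049. The SE is not too wide.

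Under blocking, the simulated power differences at R² of 0.02, 0.05 and 0.10 were 0.7, 1.3 and 3.2 points, close to the table.

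**Step 5: the SD carried forward.** Residual variance without the stratum is 1/(1 − R²) times that with it, so 2.0%, 5.3% and 11.1% too large at R² of 0.02, 0.05 and 0.10. A confirmatory sample size built on it, for an analysis that does include the stratum, is too large by the same percentages. This holds with or without blocking.

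**The case against.** The strongest reply is that the consequence is conditional, small and safe in direction. This largely stands.

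- A reader might infer that the standard errors are too wide as a matter of fact. The article does not support that. It mentions only a computer-generated list. An article may well leave out block sizes, so balance within strata can be neither assumed nor ruled out. Without it the standard error is valid.
- The stratum's remaining predictive value may be close to zero. The baseline score of the outcome and the Canadian Cardiovascular Society score probably carry part of the same information. For the SAQ angina-frequency endpoint, the baseline score measures nearly the same thing as the stratum. The article gives no figure.
- Nothing here raises the false-positive rate or biases the treatment estimate.
- Recruitment from "different clinical settings including a university hospital, a community hospital, and a cardiological clinic" might suggest that centre has been wrongly omitted too. Centre is not a stated stratification factor, so the standard-error argument does not reach it. A centre term would be an optional precision choice and is not part of this point.
- The two cut-offs might suggest that patients were placed in the wrong stratum. Nothing shows this. Both Methods sections agree, only the Abstract differs, and the envelopes came from the Centre for Clinical Studies, not from the article.

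The reply does not remove the two textual facts: the covariate list omits the only stratification factor, and the definitions of that factor disagree.

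**Conclusion.** The point holds as a modest improvement. The stated ANCOVA omits the one factor on which randomisation is stratified. The cost depends on an R² that the article does not give. Over an assumed 0.02 to 0.10, the omission forgoes about 0.5 to 2.6 points of power if strata are balanced. The standard error is then 1.0% to 5.4% too wide and type I error is 4.8% to 3.9%. With unblocked allocation within strata, precision is lost but the standard error is valid. At R² of zero there is no effect. The clearest consequence for this trial is the residual SD carried into the confirmatory design, which is overstated whenever R² is above zero. The conflict between the Abstract and the Methods over the cut-off is certain from the text, but its practical effect is not shown. None of this invalidates the trial.

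**What to change.** Add the angina-frequency stratum, as actually used to draw the envelopes, as a fixed factor in every ANCOVA in Statistical methods {20a}. Establish from the allocation list which definition was used, and reconcile the Abstract, Participant timeline {13} and Sequence generation {16a} to that one definition. The model should use the stratum recorded at randomisation, not one rebuilt later from questionnaire answers.

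The cost is one line of analysis text, one corrected definition and one degree of freedom out of about 128 evaluable patients. No new data are needed, because the stratum had to be known before an envelope could be drawn.

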The concept of placebo medicine is complex and no clear definition exists [9]. Generally speaking, placebo constitutes the substitution of the active ingredient of a therapeutic intervention through an inactive ingredient in a manner that is indistinguishable for the recipient. Even for a drug with a known mechanism of action, the drug’s pharmacological effect cannot be separated from the psychological effects of its administration and the accompanying physiological consequences [10]. Growing evidence exists for possible mechanisms of the placebo effect. Placebo interventions activate the endogenous opioid system [for review see [11]] and the dopaminergic reward circuit which is crucial for reinforcement, learning, and decision-making [for review see [11]]. Placebos also affect the autonomous nervous system for instance by altering the duration of gastric contractions [10]. The placebo effect is strongly influenced by patients’ expectations [12], learning [12], emotions [13], and personality traits such as optimism [14], empathy [12], and reward responsiveness [14].

Communication forms an essential part of the patient-doctor relationship and is key to ensure patients’ understanding of their disease and treatment and thus propagate therapy adherence. Improved communication is an important context factor often implicated as a huge contributor to the placebo effect [15]. Visualization is a good and effective means to facilitate communication and risk evaluation between patients and the physician. The VIPVIZA trial highlights the importance of the visualization of diagnostic findings to the patient [16].

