### Outcomes {12}

Symptoms such as AP according to the Canadian Cardiovascular Society score and dyspnea according to the NYHA scale will be assessed. The German version of the revised Life Orientation Test (LOT-R) [17] and the German version of the Seattle Angina Questionnaire (SAQ, CV outcomes Inc.) [18] will be filled out by the patient before randomization.

The primary endpoints are:
Change from baseline in the SAQ-derived quality of life score 1 and 6 months after PCI

The secondary endpoints are:
Change from baseline in the other SAQ-derived scores (physical limitation, angina stability, angina frequency, treatment satisfaction, disease perception)Change from baseline in the total SAQ score 1 and 6 months after PCIChange from baseline in dyspnea (NYHA score) 1 and 6 months after PCI

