Every medical encounter is characterized by a highly specific patient-clinician relationship. Although it is difficult to assess the precise effect of this relationship on medical outcomes, a meta-analysis of randomized controlled trials examining different communicational interventions found a small yet significant effect. The effect size was comparable to the reduction of myocardial infarction rates when using aspirin [15]. The placebo effect is moderated by stable personality traits such as optimism [14], empathy [12], and reward responsiveness [14], as well as transient psychological factors such as expectations [12], learning [12], or emotions [13]. Improvement of communication can positively influence these transient factors. Our study aims to elicit the placebo effect by modifying the context factors of PCI. We employ the German version of the revised Life Orientation Test [17] to assess the impact of dispositional optimism on the effect of visual demonstration.

Dyspnea is not part of the definition of angina pectoris; however, a substantial part of patients with CAD present with dyspnea as the dominant symptom together with atypical chest pain [24]. The latest update of the ESC guideline on stable CAD/CCS acknowledges this fact and highlights dyspnea as an important symptom of CAD [2, 3]. Clinical experience suggests that patients presenting with dyspnea as the main symptom are less susceptible to conventional medical or interventional treatment of CAD. This group therefore shows an increased need for additional treatment options and might especially benefit from alterations of context factors as are examined in our study design. Therefore, we additionally investigate changes of the NYHA classification at the time of both follow-ups. The time frame of the telephone interviews was chosen to assess for short-term effects after 1 month when the memory of the visual demonstration is supposedly still vivid. However, patients often do not recommence their normal daily activities directly after hospital discharge and therefore may not have had sufficient time to experience the full effects of PCI or of the visual demonstration. The 6-month interval was chosen to account for this and to measure possible lifestyle-induced changes in outcome.

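### Baseline optimism (LOT-R) is collected before randomisation but left out of the ANCOVA; adding it would be a cheap, optional gain in precision for the primary endpoints

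*Protocol article*

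**What the plan says.** Statistical methods {20a} of the protocol article gives one ANCOVA for the primary and all secondary endpoints. Treatment group and sex are fixed factors. The covariates are the baseline value of the outcome, "number of implanted stents, and baseline of Canadian Cardiovascular Society score as covariates". The list is stated as complete.

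Outcomes {12} names "The German version of the revised Life Orientation Test (LOT-R") as an instrument that patients fill out before randomisation, together with the SAQ.

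Two places give optimism a role:

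- Background and rationale {6a} has a sentence beginning "The placebo effect is strongly influenced by". It goes on to list expectations, learning, emotions and personality traits, and optimism is one of the traits.
- The Discussion says "The placebo effect is moderated by stable personality traits such as optimism", and names empathy and reward responsiveness beside it. It then gives the purpose of the LOT-R: to examine how optimism bears on the effect of showing the pictures.

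Background {6a} and the Discussion also argue that a relevant part of the symptomatic improvement after PCI may be placebo and context effect. Both arms receive PCI.

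**The concern.** The article's own reasoning has two steps. Part of the benefit of PCI is a placebo response, and optimism is among the traits that shape placebo response. Together they suggest that more optimistic patients may report better follow-up quality of life in either arm. A baseline variable with that property belongs naturally in an ANCOVA, because it removes residual variance from the treatment comparison. The model adjusts for number of stents but not for the one placebo-related trait for which the article names an instrument.

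What is at stake is precision. Sample size {14} and the Discussion both describe the pilot as a means of precise parameter estimation for a confirmatory trial, so a gain from data already in hand serves its stated purpose.

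**Working it through.** **Inputs from Sample size {14}.** The plan expects "a difference of 10 points with a standard deviation of 20 between the control and interventional groups" (d = 0.5), tested "at a two-tailed significance level of *α* = 0.05", with 80% power and 10% drop-out.

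**Reproducing the plan's figure.** The exact two-sample t-test needs 63.8, so 64 per arm, and power at 64 is 80.1%. Allowing for drop-out, 64 / 0.9 = 71.1, so 72 per arm and 144 in total. The stated numbers reproduce. The calculation takes no credit for any covariate.

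**Assumptions that the article does not supply.**

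- r is the partial correlation of LOT-R with follow-up quality of life, given the covariates already planned. It is varied over a range.
- SD 20 is read as the residual SD of the planned model.

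**Formulas.**

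- Residual SD with LOT-R = 20 × √(1 − r²).
- SE of the difference = residual SD × √(2/64). Without LOT-R this is 20 × 0.1768 = 3.54.
- Power comes from the noncentral t with noncentrality 10/SE. The planned model has six parameters, so df = 128 − 6 = 122. With LOT-R, df = 121.
- Equivalent extra evaluable patients = 128/(1 − r²) − 128.

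| Model | SE | 95% CI half-width | Power for 10 points | Equivalent extra patients |
|---|---|---|---|---|
| Planned, no LOT-R | 3.54 | 7.00 | 80.1% | n/a |
| LOT-R, r = 0.1 | 3.52 | 6.96 | 80.5% | 1.3 |
| LOT-R, r = 0.2 | 3.46 | 6.86 | 81.7% | 5.3 |
| LOT-R, r = 0.3 | 3.37 | 6.68 | 83.7% | 12.7 |
| LOT-R, r = 0.4 | 3.24 | 6.42 | 86.5% | 24.4 |

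**Cost if LOT-R predicts nothing.** One more estimated slope inflates the SE by about √(120/119) = 1.0042, or 0.4%. The table does not include this inflation. It cancels most of the 0.5% SE reduction at r = 0.1.

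**Does it matter that LOT-R is meant as a moderator?** A main-effect covariate gains according to the average of the LOT-R slopes in the two arms.

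- If the slopes are equal and opposite they cancel, and there is no gain. A simulation of that case gave an SE of 3.56 without and 3.57 with the covariate.
- If LOT-R matters only in the intervention arm, with r = 0.3 there and 0 in the control arm, the average is 0.15. The variance falls by 0.15² = 2.25%, which is about 1.1% of the SE before the 0.4% cost.
- If LOT-R matters equally in both arms, the table applies.

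**Bias check.** In simulation with a true difference of 10, the mean estimate was about 10 with and without the covariate in every case.

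**The case against.** The strongest case against is that the article never calls optimism prognostic. Its declared use for the LOT-R is effect modification, and a moderator need not predict outcome on average. This stands in part. The step from placebo response in both arms to a main effect of optimism is an inference, though a reasonable one. The claim that a moderator brings no gain holds only when the slopes in the two arms cancel.

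A second objection is that baseline quality of life, already in the model, may absorb much of any optimism effect. That also stands as a caution, and it is why r must be read as a partial correlation. The placebo argument, however, concerns change after PCI, which the baseline score need not capture.

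A third is that the same logic would bring in education, or whether pictures were already shown in the catheterization laboratory. This is fair. Covariate choice is a design option, and the planned model is legitimate as it is.

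A reader might infer four stronger things that the article does not support:

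- **That optimism is the plan's single driver of placebo response.** It is one of several influences listed.
- **That precision is certainly being lost.** That depends on a correlation the article does not give.
- **That a chance imbalance in optimism biases the result.** Over randomisations it does not, and the SE and type I error already allow for it. An imbalance at the 95% limit, 1.96 × √(2/64) = 0.35 SD, would move a single realised estimate by 0.35 × r × 20 = 0.7, 1.4 or 2.1 points at r = 0.1, 0.2 or 0.3. That is well inside the 7.0-point half-width, and it is the same lost precision seen another way.
- **That the trial is underpowered because of the omission.** The planned 80% assumes no covariate gain.

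**Conclusion.** The point holds as an optional, low-cost improvement. LOT-R is a pre-randomisation measure, the article's own argument makes it a plausible predictor of outcome in both arms, and the ANCOVA does not use it. If optimism is prognostic after the planned covariates, the gain is negligible at r = 0.1 and modest at 0.2 to 0.3: 2% to 5% off the SE, and 1.6 to 3.6 points of power. It becomes material only from about 0.4. If optimism is not prognostic, the loss is about 0.4% of the SE.

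These figures rest on 64 evaluable patients per arm, a residual SD of 20 and an assumed r. The planned analysis is neither wrong nor biased, and the stated sample size needs no change.

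**What to change.** Before the data are analysed, add the baseline LOT-R total score to the ANCOVA in {20a} as one continuous main-effect covariate for the SAQ quality-of-life primary endpoints at 1 and 6 months. State that a missing LOT-R score is replaced by the overall mean across both arms, so that no patient drops out of the analysis because of the covariate. Because the LOT-R is completed before randomisation, this fill does not depend on treatment.

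The cost is one covariate in the analysis wording, one degree of freedom and the missing-score rule. No new data and no more patients are needed. Any analysis of optimism as a modifier of the intervention effect is a separate matter and is left as it is.
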